#### Exclusion criteria

Participants will be excluded from the study if they:
(a) have severe joint pain or deformity or severe spinal deformity;(b) have serious diseases that affect mobility, such as myocardial infarction or stroke, congestive heart failure, severe chronic obstructive pulmonary disease, cancer, and other serious diseases; and(c) have had any Tai Chi training or have participated in other clinical trials.

#### Recruitment

Advertisement posters displaying the inclusion criteria will be used to recruit participants *via* WeChat. Additionally, we will conduct educational lectures about Tai Chi at the Qing Yang District University for the Elderly and Ci Tang Street Community to raise awareness and attract qualified participants. Eligible participants will provide written informed consent.

### Procedures

#### Randomization and blinding

Eligible participants will be randomly assigned to two groups in a 1:1 ratio. Randomization will be performed by an independent researcher and will be generated in blocks of varying sizes and stratified according to the central computer system. The group assignments will be hidden in opaque envelopes by an independent researcher who will not participate in the study. The envelopes will be opened for each participant after the completion of the assessments. The instructors and participants will not be blinded to the group assignments. Research assessors and statisticians will be blinded to group allocation.

### Interventions

#### Tai Chi group

Participants in the Tai Chi group will attend a Yang-style 24-form Tai Chi training program. Each Tai Chi session will last 60 min (10 min warm-up, a 40 min Tai Chi training program, and a 10 min cooldown) three times a week for 8 weeks. The training sessions will be conducted by three experienced instructors.

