### Participants

#### Sample size

This study will be designed to compare the effectiveness of the Tai Chi group against the control group. Sample size calculations will be based on the change in the Pittsburgh Sleep Quality Index (PSQI) and the Visual Analog Scale (VAS) scores. The study will detect a 5-point difference between groups on the PSQI scores (Irwin et al., 2008) and a 1.96-point difference in the VAS scores (Bower and Irwin, 2016). A total sample size of 96 participants will achieve 90% power with an alpha of 0.05. However, considering a 10% drop rate, we plan to recruit 106 patients.

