#### Control group

The participants in the control group will not receive any interventions for 8 weeks. After 8 weeks, participants will be instructed to do Tai Chi exercises for 8 weeks for 60 min (10 min warm-up, a 40 min Tai Chi training program, and a 10 min cooldown) three times a week. Tai Chi group coaches will also instruct participants.

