### Statistical analysis

The statisticians and researchers will establish a statistical plan. It will contain baseline characteristics, treatment effects, adverse events, and attendance evaluations. All analyses will be conducted using the intention-to-treat method. Two independent sample t-tests will be used for analysis. Repeated measures analysis of variance will be used to examine the effects of VAS between the Tai Chi group and the control group. We will use the Wilcoxon-Signed Rank Test to assess non-normally distributed data. Continuous data will be expressed as mean ± standard deviation. The chi-square test will be used for categorical data. We will set the statistical significance at a *P*-value of < 0.05. Missing data will be processed according to the last observation carry-forward rules. We will use IBM SPSS Statistics version 25 (SPSS, Inc., USA) for data analysis.

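### The week-8 analysis treats Tai Chi participants as independent although only that arm is trained in instructor-led sessions; any class or instructor correlation would make the standard error too small.

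*Protocol article*

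**What the plan says.** All references are to the protocol article.

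- **Randomization and blinding:** participants are randomised individually, 1:1. Assessors and statisticians are to be blinded to allocation.
- **Tai Chi group:** an 8-week programme with three 60-minute sessions per week. On who teaches it, the section says "The training sessions will be conducted by three experienced instructors", and nothing more.
- **Control group:** the waiting period is described thus: "The participants in the control group will not receive any interventions for 8 weeks". They then follow the same programme for 8 weeks, and "Tai Chi group coaches will also instruct participants".
- **Sample size:** "Sample size calculations will be based on the change in the Pittsburgh Sleep Quality Index (PSQI) and the Visual Analog Scale (VAS) scores". The target differences are given as "The study will detect a 5-point difference between groups on the PSQI scores" and "a 1.96-point difference in the VAS scores". Then: "A total sample size of 96 participants will achieve 90% power with an alpha of 0.05". A 10% allowance for dropout brings the number to 106. No SD, ICC, cluster size or design effect appears.
- **Statistical analysis:** "Two independent sample t-tests will be used for analysis". VAS is also analysed by repeated measures ANOVA. Neither analysis is given a class, instructor or site term.
- **Attendance rate:** sign-in sheets are already planned.

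The article does not say how many classes will run, whether a participant stays with one instructor, or whether instructors rotate or teach together.

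**The concern.** Individual randomisation makes the two arms comparable at baseline. It does not keep outcomes independent once one arm is treated together. Over 8 weeks the Tai Chi participants attend 24 led sessions (3 x 8). A shared teaching style, encouragement and group company can make their outcomes resemble one another, and both primary outcomes are self-reported. Controls have no such shared exposure before week 8, so up to that point the design is partially nested: any clustering lies in one arm only.

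A t-test or repeated measures ANOVA with no class or instructor term counts each Tai Chi participant as a full independent observation. If there is positive correlation within classes or instructors, the uncertainty of the Tai Chi mean is understated, confidence intervals are too narrow and the nominal 5% error rate is exceeded. Week 8 is where this matters most, because it is the one assessment after baseline at which a treated arm is compared with an arm that has not yet been treated.

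**Working it through.** **Inputs.** From the article: 96 evaluable participants, so 48 per arm at 1:1; 90% power; alpha 0.05; differences of 5 (PSQI) and 1.96 (VAS); three instructors. Assumed because the article does not give them: a two-sided test; ICC of 0.01, 0.02, 0.05 or 0.10; cluster size m = 16 (48/3, each participant staying with one instructor) or m = 8 (six classes).

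**Step 1: the plan's own figure.** The 96 cannot be reproduced, because no SD is stated. Solved backwards with the normal approximation:

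- standardised difference = (1.960 + 1.282) x sqrt(2/48) = 0.66
- implied SD = 5/0.66 = about 7.6 for PSQI, and 1.96/0.66 = about 2.96 for VAS

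The step to 106 is dropout alone: 96 x 1.10 = 105.6, rounded up to 106. No further allowance is visible.

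**Step 2: clustering in one arm.**

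- design effect in the Tai Chi arm: DE = 1 + (m - 1) x ICC
- ratio of correct to unadjusted standard error: r = sqrt((DE + 1)/2)
- type I error of the unadjusted test: 2 x [1 - Phi(1.960/r)]
- power with the correct standard error, if 96 is exactly 90% under independence: Phi(3.242/r - 1.960)

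Example, m = 16 and ICC 0.05: DE = 1 + 15 x 0.05 = 1.75; r = sqrt(2.75/2) = 1.17; type I error 9.5%; power 78.9%.

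| m | ICC | DE | r | Type I error | Power |
|---|---|---|---|---|---|
| 16 | 0.01 | 1.15 | 1.04 | 5.9% | 87.8% |
| 16 | 0.02 | 1.30 | 1.07 | 6.8% | 85.6% |
| 16 | 0.05 | 1.75 | 1.17 | 9.5% | 78.9% |
| 16 | 0.10 | 2.50 | 1.32 | 13.8% | 68.8% |
| 8 | 0.01 | 1.07 | 1.02 | 5.4% | 89.0% |
| 8 | 0.02 | 1.14 | 1.03 | 5.8% | 88.0% |
| 8 | 0.05 | 1.35 | 1.08 | 7.1% | 84.9% |
| 8 | 0.10 | 1.70 | 1.16 | 9.2% | 79.7% |

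Simulating the t-test itself (40,000 trials per setting, clusters of m against 48 independent controls) agrees with the type I error column to within about half a percentage point. The power column uses normal critical values and makes no deduction for having few clusters.

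**Step 3: how far the power column depends on the unstated SD.** Power = Phi(difference/(SD x sqrt((DE + 1)/48)) - 1.960). With m = 16:

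- PSQI SD 5: 99.7% at ICC 0.01, 96% at ICC 0.10
- VAS SD 2.0: 99.6% at ICC 0.01, 95% at ICC 0.10
- VAS SD 2.5: 96% at ICC 0.01, 91% at ICC 0.05, 83% at ICC 0.10

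At ICC 0.10, power stays at or above 90% when the SD is at most 5/(3.242 x sqrt(3.5/48)) = 5.7 for PSQI, or 1.96/(3.242 x sqrt(3.5/48)) = 2.2 for VAS. The type I error column does not involve the SD, so a smaller SD does not repair it.

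**The case against.** **The cluster structure is not in the text.** Naming three instructors does not mean three groups of 16. Rotation or joint teaching fits the wording equally well. The class would then be the cluster, and its size is not given. This stands, and it is why both cluster sizes are shown and why the fix uses the class.

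**A reader might infer that the stated 90% power is too high.** The article does not support that. With neither SD nor ICC stated, the 96 cannot be checked, and Step 3 shows that a smaller SD would offset the loss. All that can be said is that no allowance for clustering is visible.

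**The error rate depends on the target.** For the effect as delivered by these three instructors, instructor differences are fixed and do not inflate the test's error. If Tai Chi had no effect under any instructor, only shared class influences would remain. This narrows the point but does not remove it: class-level correlation remains possible, and the article does not confine its conclusion to these instructors.

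**The analysis plan may deal with it.** The article promises a statistical plan, which is not shown, and model detail properly belongs there. But the article does name its tests and does state power at 96. A later plan can add a model, but the sample size has already been set with no visible allowance.

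**The imbalance is temporary.** After week 8 the same coaches teach the controls, so clustering confined to one arm does not describe weeks 16 to 40. This stands, and the point is limited to week 8.

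**Conclusion.** The concern holds conditionally. The design delivers led group training to one arm only up to week 8, and the stated tests and sample size treat all participants as independent. If outcomes correlate within class or instructor, the week-8 standard error is too small. For ICC 0.01 to 0.10 the correct standard error is 4% to 32% larger with 16 per cluster and 2% to 16% larger with eight. The type I error is about 6% to 14% and about 5% to 9% respectively.

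These sizes rest on assumed ICCs and cluster sizes, on participants staying within one cluster, and on a conclusion meant to reach beyond the particular classes and instructors used. A shortfall from 90% power is not established. A sensitivity analysis is proportionate; the evidence does not call for a new primary analysis or a larger trial.

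**What to change.** 1. State how participants are divided among instructors and classes, and record both for each participant on the existing sign-in sheets, from the first session.
2. Pre-specify one sensitivity analysis of PSQI and VAS at week 8: a partially nested mixed model with class as the cluster in the Tai Chi arm only, controls independent, and small-sample (Satterthwaite) degrees of freedom. Class is preferable to instructor, because three instructors leave only about 2 degrees of freedom for the variance between them.
3. If there are too few classes to estimate that variance, report instead the week-8 confidence interval over a fixed ICC range, for example 0.01 to 0.10.
4. Add a sentence to the Sample size section that the 90% power assumes no clustering by class or instructor.

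The cost is small: two fields on a form already in use, one additional analysis and a few sentences, with no added participants. There are two downsides. The sensitivity interval will be wider than the main one. And because class labels exist only in the Tai Chi arm up to week 8, they reveal allocation, so this analysis should be run after the blinded main analysis is complete.

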#### Control group

The participants in the control group will not receive any interventions for 8 weeks. After 8 weeks, participants will be instructed to do Tai Chi exercises for 8 weeks for 60 min (10 min warm-up, a 40 min Tai Chi training program, and a 10 min cooldown) three times a week. Tai Chi group coaches will also instruct participants.

### Outcome measurements

#### Primary outcomes

##### Sleep

The primary outcome is the PSQI (Pittsburgh Sleep Quality Index) scores, which are the most commonly used measure of sleep quality and consist of 19 questions about sleep habits over a 1-month period (Nadal-Nicolas et al., 2020). The PSQI measures sleep quality, sleep latency, sleep duration, habitual efficiency, disturbances, use of sleeping medications, and daytime dysfunction (Pachikian et al., 2021). The scores range from 0 to 21, with higher scores indicating worse sleep quality. A score >5 indicates clinical sleep impairment (Kalmbach et al., 2020).

##### Pain intensity

The VAS (Visual Analog Score) is a commonly used tool for evaluating back pain. The scale ranges from 0 to 10 (Shu and Zhang, 2022), with a higher score indicating greater pain intensity. Participants will be asked to rate their pain weekly before follow-up, and the levels of pain intensity will be categorized as none (0), mild (1–3), moderate (4–6), and severe (7–10) (Liu et al., 2022).

#### Secondary outcomes

##### Quality of pain

The quality of pain will be assessed using a pain diary, which consists of the frequency and duration of pain. Patients will be instructed to maintain a daily log of the frequency of their pain and the number of times they experience it. We will monitor participants' use of the telephone to write pain diaries.

##### Range of motion

The range of motion includes lumbar flexion, extension, and right and left lateral flexion; lumbar spine rotation will be measured using a goniometer (Dayanir et al., 2020; Ricci et al., 2022). The participants will be asked to bend forward and backward into full lumbar flexion. We will measure the lateral flexion from the finger to the floor at the maximal degree (Elshiwi et al., 2019). The participants will be instructed not to move the waist and to minimize rotation as much as possible.

##### Physical performance

Physical performance will be measured using the Japanese Orthopedic Association Score (JOA, range 0–29, with higher scores indicating a greater function), the Oswestry Disability Index (ODI, range 0–100, with higher scores indicating a worse impact on life), and the Chronic Pain Self-Efficacy Scale (CPSS, range 0–110, with higher scores indicating a greater confidence in performing physical activities). The JOA score has been widely used to assess function after intervention for low back pain (Ma et al., 2021). It consists of subjective symptoms, clinical signs, daily activities, and bladder function (Tsukayama et al., 2002). The questionnaire includes 10 categories: waist and leg pain, personal life care, lifting heavy objects, walking, standing, sitting, sleeping, sexual life, social life, and travel (Marti-Salvador et al., 2018). The CPSS will be used to assess the participants' perceived self-efficacy in coping with chronic pain (Anderson et al., 1995). This scale contains self-efficiency for pain management (PSE), self-efficiency for physical function (FSE), and self-efficiency for symptoms and coping with symptoms (CSE).

##### Social support

Social support will be assessed using the Social Support Rating Scale (SSRS). Social support evaluations include objective support, subjective support, and utilization of social support. Higher scores indicate greater social support.

##### Quality of life

The participants' health status will be assessed with Short Form 36 (SF-36), which ranges from 0 to 100, with higher values indicating better general health status (Mahdavi et al., 2022). The questionnaire contains sections on physical functioning (PF), role-physical (RP), bodily pain (BP), general health (GH), vitality (VT), social functioning (SF), role-emotional (RE), mental health (MH), and health transition (HT) (Huang et al., 2019).

##### Monitoring of adverse events

The participants will be asked about the occurrence of adverse events during the observation period. We define adverse events as increased pain, falling, disability, life-threatening events, and any events related to Tai Chi. If sleep and pain continue to worsen, a medical diagnosis shall be made as soon as possible, and the clinical trial may be terminated.

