## Methods

### Study design

This study design conducts an open-label, randomized, controlled trial. The study protocol was approved by the Ethics Committee of the Hospital of Chengdu University of Traditional Chinese Medicine in Sichuan Province on 06/06/2022 (ethics approval number: 2022KL-038-02). This trial is registered with the Chinese Trial Registry under the number ChiCTR2200064977. This protocol adheres to the Consolidated Standard of Reporting Trials (CONSORT) and the Standard Protocol Items: Recommendations for Interventional Trials (SPIRIT). This study will be conducted at the Hospital of Chengdu University of Traditional Chinese Medicine, Qing Yang District University for the elderly, and Ci Tang Street Community. We will compare the effects of the Tai Chi group against the control group on insomnia in elderly people with CNLBP. Baseline assessments and follow-up assessments will be conducted at weeks 8, 16, 32, and 40 to measure primary outcomes such as sleep and pain intensity as well as secondary outcomes such as quality of pain, range of motion, physical performance, social support, quality of life, attendance rate, and adverse events. The detailed schedule of patient interventions and outcomes is described in Table 1.

**Table 1 T1:** Schedule of patients, intervention, outcomes.

**Item**	**Week 0**	**Week 1–8**	**Week 8**	**Week 9–16**	**Week 16**	**Week 32**	**Week 40**

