**Outcomes**							
PSQI	×		×		×	×	×
VAS	×	×	×	×	×	×	×
Quality of pain	×		×		×	×	×
Range of motion	×		×		×	×	×
JOA	×		×		×	×	×
ODI	×		×		×	×	×
CPSS	×		×		×	×	×
SSRS	×		×		×	×	×
SF-36	×		×		×	×	×
Adverse events			×		×	×	×
Attendance rate			×		×	×	×

PSQI, Pittsburgh Sleep Quality Index; VAS, Visual Analog Score; JOA, Japanese Orthopedic Association Scores; ODI, Oswestry Disability Index; CPSS, Chronic Pain Self-Efficacy Scale; SF-36, Short Form 36; SSRS, Social Support Rating Scale.

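### Adverse events are scheduled only at weeks 8, 16, 32 and 40, so falls and other non-pain events during either arm's training have no stated interim record

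*Protocol article*

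**What the plan says.** Table 1, titled "Schedule of patients, intervention, outcomes", has separate columns for the assessment visits (weeks 0, 8, 16, 32 and 40) and for the two training periods (weeks 1–8 and weeks 9–16). The row "Adverse events" is marked at weeks 8, 16, 32 and 40 and nowhere else. The VAS row is marked in every column, including both training periods.

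The text under Study design agrees with the table: "Baseline assessments and follow-up assessments will be conducted at weeks 8, 16, 32, and 40", and adverse events are listed among the outcomes measured there.

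The section Monitoring of adverse events says that "The participants will be asked about the occurrence of adverse events during the observation period". The definition that follows is "We define adverse events as increased pain, falling, disability, life-threatening events, and any events related to Tai Chi". The section then adds: "If sleep and pain continue to worsen, a medical diagnosis shall be made as soon as possible, and the clinical trial may be terminated". It does not say how often participants are asked, by whom, or what happens when someone stops attending.

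For pain there is more. Under Pain intensity, "Participants will be asked to rate their pain weekly before follow-up". Under Quality of pain, participants keep a daily log, with monitoring by telephone. Under Attendance rate, instructors use sign-in sheets. Under Data collection, participants are to be contacted when outcome data are missing.

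**The concern.** The Tai Chi arm trains only in weeks 1–8 and the control arm only in the 8 weeks after that. Those are the periods in which exercise-related harm would occur, and weeks 1–8 are also the only period in which Tai Chi is compared with no Tai Chi. A schedule that first asks about events at week 8 asks the Tai Chi arm once its programme is over.

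Two things are at stake. The first is completeness. A fall early in training must be remembered for up to 8 weeks, and a participant who falls and leaves before week 8 does not reach the first scheduled question. The second is fit with the protocol's own monitoring section, which foresees prompt action if sleep and pain keep worsening and so presupposes some information between visits. Pain has that information. Sleep (PSQI) and non-pain events have none scheduled.

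**Working it through.** **1. Collection points and gaps.** From Table 1 the adverse-event marks are at weeks 8, 16, 32 and 40, counted from week 0:

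- 8 − 0 = 8 weeks
- 16 − 8 = 8 weeks
- 32 − 16 = 16 weeks
- 40 − 32 = 8 weeks

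**2. Exposure between the points.** From Interventions, three sessions a week for 8 weeks gives 3 × 8 = 24 sessions per arm.

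- The Tai Chi arm's 24 sessions all lie between week 0 and the week-8 mark.
- The control arm's 24 sessions all lie between the week-8 and week-16 marks.
- The 16-week gap follows scheduled training in both arms, so it says little about events during sessions. The recall window that matters for training is 8 weeks.

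**3. What is recorded between visits.**

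| Item | Table 1, training columns | Interim method stated in the text |
|---|---|---|
| VAS | marked | weekly rating |
| Quality of pain | blank | daily log with telephone monitoring |
| Attendance | blank | sign-in sheets kept by instructors |
| Adverse events | blank | none |

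A blank training column does not by itself prove that nothing is gathered in training, because quality of pain and attendance are also blank there. But each of those has a method in the text that fills the blank, and adverse events do not. Increased pain can be read from the VAS and the diary. Falls, disability and other events have no interim source.

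**4. Early leavers.** The sample size section plans for loss by "considering a 10% drop rate". With 53 per arm, 0.10 × 53 = 5.3, or about 5 participants per arm. The article gives neither timing nor reason for this loss, so the number who leave before week 8, and the number who leave because of an event, cannot be worked out.

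**5. What recall could do (illustration only).** The document gives no figure for recall. Assume a constant event rate and that a proportion r of events is still remembered after each further week. The share reported at a visit n weeks after the last one is then (1/n) × (r⁰ + r¹ + … + rⁿ⁻¹). For n = 8:

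- r = 1.00: 100%
- r = 0.98: 93%
- r = 0.95: 84%
- r = 0.90: 71%

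The result runs from no loss to a sizeable one, depending wholly on r. It does not estimate an under-count in this trial.

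**The case against.** The strongest reply is that Table 1 may show when events are summarised, not the only times they are asked about. Attendance carries the same four marks and is logged at sessions. Quality of pain is likewise unmarked in the training columns and is logged daily. The wording on the observation period is open to continuous asking, instructors see trainees three times a week, and a journal article may leave the detail of event elicitation to the full protocol.

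Much of this stands. It is why the point concerns what is scheduled and stated, and not what staff will in fact do. It does not remove the point. The article goes beyond silence: it fixes a schedule, uses the training columns where interim collection is meant for the VAS, leaves them blank for adverse events, and repeats the visit weeks in the text. Contact for missing outcome data is retrospective and names neither adverse events nor withdrawal.

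A reader might infer several stronger things that the document does not support:

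- **That safety results will be biased in favour of Tai Chi.** Both arms share one schedule, so the schedule alone does not create unequal ascertainment. That reading needs harm-driven loss from the Tai Chi arm, whereas the only dropout risk named in the Discussion is in the waiting period, which concerns the control arm.
- **That pain flares go uncounted.** Pain is recorded weekly and daily. What is unclear is whether those records count as adverse events.
- **That 2% to 6% of the Tai Chi arm would have an unrecorded event.** This is 1/53 = 1.9% to 3/53 = 5.7%, which merely restates an assumption that 1 to 3 people leave by week 8 because of an event.
- **That events come to light too late for anyone to act.** The article does not say that events reported to instructors are ignored.

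**Conclusion.** The point holds as a gap in the stated schedule. No adverse-event collection is marked in either training period, no interim method is given, and falls and other non-pain events therefore rest on recall of up to 8 weeks, with possible loss in participants who leave before week 8. For increased pain the gap is narrower: the data exist, but their link to the adverse-event count is not stated.

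The size and direction of any under-count cannot be derived from the document. The conclusion assumes that the marks in Table 1 mean what they mean for the VAS row. If events are in fact asked about continuously, the remedy reduces to saying so and correcting the table. The point concerns the safety reporting and does not touch the analysis of sleep or pain. It is worth changing because events not recorded during training may not be recoverable later.

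**What to change.** - Mark adverse events in the weeks 1–8 and weeks 9–16 columns of Table 1.
- With each weekly VAS rating, ask both arms the same short event question, naming falls and recording the date of the event.
- Ask it once more when a participant withdraws.
- State in Monitoring of adverse events whether worsening on the VAS or in the pain diary counts as an adverse event.
- Keep the questions at weeks 8, 16, 32 and 40.
- Reconcile the section's provision for continued worsening of sleep and pain with the times at which that information is scheduled.

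The cost is slightly more data collection. Recorded rates of minor events will also rise, which the report should explain. One practical condition applies: the article does not state how the weekly VAS rating is obtained, so whatever route is used must also be able to carry the event question. It cannot be taken for granted that a staff contact already exists each week.

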**Methods:**

The study design will be a randomized, controlled, open-label trial. Participants (*n* = 106) will be recruited from the Hospital of Chengdu University of Traditional Chinese Medicine, Qing Yang District University for the Elderly, and Ci Tang Street Community. Participants will be randomly assigned to the Tai Chi group (*n* = 53) and the control group (*n* = 53). The Tai Chi group will undergo a Yang-style 24-form Tai Chi program for 8 weeks. The control group will have a waiting period of 8 weeks, followed by 8 weeks of Tai Chi practice. The primary outcomes of this study will be changes in sleep quality and pain intensity. Secondary outcomes of interest will include changes in the quality of pain, range of motion, physical performance, social support, and overall quality of life. Any adverse events and attendance rates will also be reported in this study.

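### The adverse-event definition includes a Tai Chi-related class that the waiting-list arm cannot have before week 9, and it leaves out other unattributed events in both arms

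*Protocol article*

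**What the plan says.** The definition is in the protocol article, Secondary outcomes, Monitoring of adverse events: "We define adverse events as increased pain, falling, disability, life-threatening events, and any events related to Tai Chi". The same paragraph says how events are found: "The participants will be asked about the occurrence of adverse events during the observation period". It exempts neither arm from that question.

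The abstract promises: "Any adverse events and attendance rates will also be reported in this study". The Study design section lists adverse events among the secondary outcomes, Table 1 schedules them at weeks 8, 16, 32 and 40, and the Statistical analysis section says the statistical plan will cover them.

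Exposure differs by arm. For the Tai Chi group: "The Tai Chi group will undergo a Yang-style 24-form Tai Chi program for 8 weeks", which Table 1 places in weeks 1–8. For the control group: "The participants in the control group will not receive any interventions for 8 weeks", and then "After 8 weeks, participants will be instructed to do Tai Chi exercises for 8 weeks for 60 min", which Table 1 places in weeks 9–16.

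**The concern.** Four of the five classes describe what happened to the participant. The fifth describes what caused it, and the cause is the randomised treatment. Whether an event enters the count therefore depends partly on the arm the person is in.

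This has two consequences. First, between randomisation and week 8 the fifth class is open to one arm only. After week 8 the waiting-list arm starts Tai Chi, so no later period compares Tai Chi with an arm never exposed to it. Second, an event outside the four named types that nobody links to Tai Chi is, by this definition, not an adverse event. A non-life-threatening hospital admission is an example. Participants are aged 60 to 75, so some illness unrelated to the programme is to be expected in both arms.

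What is at stake is the reading of the arm-level harm counts for a named secondary outcome. The control arm is there to show the background rate of such events, and for events outside the named types the definition removes that background. Neither primary outcome is affected.

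**Working it through.** **Inputs from the protocol article.** The five-class definition (Monitoring of adverse events); no intervention for controls for 8 weeks and Tai Chi afterwards (Control group, Table 1); Tai Chi in weeks 1–8 for the other arm (Tai Chi group, Table 1); 53 per arm (Abstract). The article gives no adverse-event rate, so there is no figure of its own to reproduce.

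**Step 1: apply the definition to weeks 0–8.**

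| Event | Tai Chi arm | Waiting-list arm |
|---|---|---|
| One of the four named types | counted | counted |
| Any other event, attributed to Tai Chi | counted | cannot arise |
| Any other event, not attributed | not counted | not counted |

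The asymmetry is in the second row and the loss in the third. Nothing elsewhere in the article widens the definition.

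**Step 2: illustrate the size on assumed rates.** Let pL be the risk of a named-type event and pO the risk of any other event. Both are taken as equal in the two arms (no true harm) and independent of each other. Let a be the share of other events in the Tai Chi arm that are attributed to Tai Chi. All three are assumptions.

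- Counted, waiting list: pL
- Counted, Tai Chi: 1 − (1 − pL)(1 − a·pO)
- True all-event risk, each arm: 1 − (1 − pL)(1 − pO)
- Spurious difference: (1 − pL)·a·pO

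With pL = 0.05 and pO = 0.20, the true risk is 1 − 0.95 × 0.80 = 0.240 in each arm, or 12.7 of 53. The waiting-list count is 0.05 × 53 = 2.7, so 53 × (0.240 − 0.050) = 10.1 people with an event go uncounted there.

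| a | Tai Chi arm, counted | Waiting list, counted | Uncounted, Tai Chi | Uncounted, waiting list |
|---|---|---|---|---|
| 0 | 5.0% (2.7 of 53) | 5.0% (2.7 of 53) | 10.1 | 10.1 |
| 0.25 | 1 − 0.95 × 0.95 = 9.8% (5.2) | 5.0% (2.7) | 7.6 | 10.1 |
| 0.50 | 1 − 0.95 × 0.90 = 14.5% (7.7) | 5.0% (2.7) | 5.0 | 10.1 |
| 1.00 | 1 − 0.95 × 0.80 = 24.0% (12.7) | 5.0% (2.7) | 0 | 10.1 |

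Over pL from 5% to 10%, pO from 10% to 30% and a from 0.25 to 1, the spurious difference runs from 0.90 × 0.25 × 0.10 = 2.25 percentage points to 0.95 × 1 × 0.30 = 28.5 percentage points. With a = 0 it is zero, but the other events are lost in both arms.

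**Step 3: the same case with a cause-neutral definition.** Both arms are expected to show 24.0%, so the expected difference with no true harm is 0.

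No false-positive probability is given here, because the article ties no between-arm test to adverse events.

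**The case against.** The strongest reply is that the named types cover the obvious harms of exercise in older people with back pain, apply equally in both arms and can be compared over weeks 0–8. That stands. A reader might infer that the whole safety comparison is invalid, but the document does not support this: the imbalance comes from the fifth class alone. If events are tabulated by class, the Tai Chi-related row can be read for what it is. Even then, the control arm has no corresponding row, and unattributed other events are missing from both arms.

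It is also fair to say that the article states no between-arm safety test. It says only that adverse events will be reported and covered in the statistical plan. A comparison by arm is a natural use of a secondary outcome in a two-arm trial, but it is an inference.

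Four further readings are tempting and should not be pressed.

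- **Unblinded attribution.** The article says "The instructors and participants will not be blinded to the group assignments", but the same section keeps assessors and statisticians blinded, and the article does not say who decides whether an event is related to Tai Chi. Blinding would not cure the problem in any case, because the class itself depends on exposure.
- **Recall over 8 to 16 weeks.** Table 1 marks adverse events at weeks 8, 16, 32 and 40. That these are the only enquiries is an inference, since the text speaks of asking during the observation period.
- **Existing weekly contacts.** The article says "Participants will be asked to rate their pain weekly before follow-up". That establishes a weekly rating, not a weekly contact with staff.
- **A contradiction with the abstract.** The abstract's promise can be read as covering any event that meets the definition. The definition is narrower than a plain reading of the abstract, and no more than that can be claimed.

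Finally, causality and seriousness fields are commonly left to a fuller protocol or the case report form. Their absence is not the point. The point is the definition that the article does state.

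**Conclusion.** The concern holds in a limited form. As written, the definition is asymmetric in one of its five classes during weeks 0–8, and it excludes from both arms any event that is neither a named type nor attributed to Tai Chi. Both statements follow from the wording and the exposure schedule and need no numerical assumption.

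The size is unknown. The percentages above rest entirely on assumed event rates and attribution shares, with no true harm, and show only how the mechanism works. If some attributed events really are caused by Tai Chi, part of the excess is real, but the control arm cannot supply the background against which to judge it.

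The document does not support saying that the trial's safety statement cannot be trusted at all. It supports saying that the total count by arm would be incomplete and, outside the four named types, not comparable. This is worth correcting as a stated rule that works badly.

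**What to change.** Define an adverse event as any untoward medical occurrence in either arm, whatever its cause. Record relatedness and seriousness as separate attributes of each event. Put the same question to both arms at the scheduled assessments, and alongside the weekly VAS rating if that rating involves contact with the participant. Report all events by arm for weeks 0–8, with falls and increased pain shown separately, and report later periods by arm with the control group's start of Tai Chi made clear. Bring the abstract and the definition into line.

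The cost is a change of wording in the protocol and case report form, and more minor events to record. The change concerns what is counted and how it is labelled; it alters nothing in the clinical management of participants.
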